### Monitoring

Before intervention implementation, the researcher used 2 days to train nurses and therapists on all aspects of parent recruitment, data collection, and the treatment protocol. During the intervention process, regular monthly discussions will be conducted within the intervention team to facilitate effective communication and propose resolution of any issues encountered during the intervention.

## Discussion

This study protocol describes the theoretical basis and design of a quasi-experimental study that evaluated the effects of a health education program targeting parental self-efficacy for children with ASD. Early intervention is important for children with ASD, and if the intervention proves to be effective, it will provide important insight into promoting parents’ treatment compliance in early intervention. Improving parental self-efficacy is crucial to improving treatment compliance, FQoL, and reducing parenting stress in parents of children with ASD. Although developed and tested in a Chinese tertiary center, the barriers that lack of parental confidence, skills for home intervention are widely reported across different health system (2). Our results will be applicable for generalization to countries which has limited ASD-related resources.

### Ethics and dissemination

This study is not expected to cause any physical harm for both caregivers and children given the nature of health education. Participants may experience transient fatigue during the program. Researchers are trained to assess participants’ condition and response to fatigue. We will pause education or arrange referral if needed. Adverse events will be recorded and reviewed by the PI within 72 hours. The study protocol will follow the ethical principles outlined by the Helsinki Declaration. Ethics approval has been obtained from the Medical Ethics Committee of the Third Affiliated Hospital of Sun Yat-sen University (No. [2022]02-270-01) prior to the commencement of the study. The eligible parents will be provided with comprehensive information about the purpose, significance, and process of the study before the intervention. Parents will sign informed consent forms and have the right to withdraw from the study at any time. Their decision to withdraw will not affect their subsequent treatment. Additionally, the control group will receive a book valued at 50 CNY at the end of the study. The study protocol will also be available to the parents in the control group.

### Limitations

This study has several limitations. First, this study uses a non-randomized design due to high contamination risk and operational constraints in a single ward. This may increase bias to unbalanced baseline characteristics and susceptibility to secular trends. We will mitigate this via standardized delivery and covariate-adjusted GEE models. Second, the study was conducted at a single center, which may limit the generalizability of the findings to a broader population of parents of children diagnosed with ASD. Third, blinding the intervention practitioners and participants is not feasible due to the nature of the health education program. To mitigate potential bias, data analysts will be blinded. Fourth, this study has not conducted in-depth semi-structured interviews, future studies need to incorporate a planned qualitative interview to deepen understanding of intervention effects.

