## Methods

### Study design

This study protocol outlines a single-center, pre-test, post-test, double-arm quasi-experimental trial with a 1:1 ratio. Randomized controlled trial was deemed infeasible in this setting because concurrent enrollment to parallel arms would likely result in contamination in shared ward and the same nurse educators. The Standard Protocol Items: Recommendations for Interventional Trials can be found in Supplementary File 1. The control group received routine care, and the intervention group received a 1-month self-efficacy promotion program on the basis of usual care. **Table 1** summarizes the program of enrollment, intervention and evaluation. The study has been registered at the Chinese Clinical Trial Registry (23/05/2023, No. ChiCTR2300071721).

**Table 1 T1:** Protocol schedule of enrollment, interventions, and assessments.

Time point	Pre-intervention screening/consent	Allocation	Baseline measurement	PSE promotion intervention	Post-intervention Measurement	Follow-up measurement
	-T1	0	T0	Intervention	T1	T2
Eligibility screen	×					
Informed consent	×					
Allocation		×				
Intervention group			×	×	×	×
Control group			×		×	×
Descriptive characteristics						
Sociodemographic characteristics			×			
ASD-related characteristics			×			
PSOC			×		×	×
PSI-SF			×		×	×
TCS			×		×	×
FQoL			×		×	×
ABC			×			×

ABC, Autism Behavior Checklist; FQoL, Beach Center Family Quality of Life Scale; PSE, Parenting self-efficacy; PSI-SF, Parenting Stress Index-Short Form; PSOC, Parenting Sense of Competence Scale; TCS, Treatment Compliance Scale for Children with Autism Spectrum Disorder.

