### Study setting and population

The study is conducted at the child development behavior center of a tertiary hospital in southern China. This center provides ASD diagnosis and structured interventions. Hospitalization is used to provide diagnostic assessment for children with ASD and initiate parent-mediated intervention for children with ASD. The typical hospitalization period is 7 to 14 days. The target population consists of parents of children who have recently been diagnosed with ASD. The study conducted from October 2022 to May 2024. Participants recruited from October 2022 to March 2023 were assigned to the control group, while participants recruited from April to October 2023 were assigned to the intervention group.

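### Arm coincides exactly with enrolment period, so covariate-adjusted GEE and standardised delivery cannot mitigate a secular trend in post-baseline change, as the Limitations section says they will

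*Protocol article*

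**What the plan says.** **Design.** The Study design section describes a "single-center, pre-test, post-test, double-arm quasi-experimental trial with a 1:1 ratio". It gives the reason for not randomising: "concurrent enrollment to parallel arms would likely result in contamination in shared ward and the same nurse educators".

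**Allocation.** The section on study setting and population states that "Participants recruited from October 2022 to March 2023 were assigned to the control group", and that "participants recruited from April to October 2023 were assigned to the intervention group".

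**Analysis.** Statistical methods plans a GEE model for group and time differences. An adjusted version draws on sociodemographic or clinical characteristics with P<0.01 at baseline. Time here means assessment visit (T0, T1, T2 in Table 1). No calendar-time term is named.

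**Limitations.** The non-randomised design is said to raise the risk of baseline imbalance and a second problem, followed at once by the remedy for both: "susceptibility to secular trends. We will mitigate this via standardized delivery and covariate-adjusted GEE models".

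**The concern.** The remedy is offered for two different problems, baseline imbalance and secular trends. Covariate adjustment is a reasonable partial answer to the first. For the second, a model needs some information on what happens in each arm in the same period, and this design provides none.

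What is at stake is how a group difference in C-PSOC may be read. If parents in the later period would have improved more (or less) anyway, that difference goes into the estimated programme effect. A reader who relies on the Limitations section would believe the analysis had dealt with this.

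**Working it through.** The protocol gives no figure for a secular trend, so there is none to reproduce. The shift sizes below are assumptions.

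**1. Overlap.** Controls: October 2022 to March 2023 (6 months). Intervention: April to October 2023 (7 months). Shared recruitment months: 0. Arm is fixed by enrolment date.

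**2. Can a period factor be fitted?** Intercept + arm + period gives a design matrix of rank 2 with 3 columns. With visits added (arm-by-visit and period-by-visit), the rank is 6 with 9 columns. No arm contrast can be separated from the matching period contrast.

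**3. Can a linear date term be fitted?** Yes, but only by extrapolating each cohort's slope into months where the other arm has no data. Assuming even accrual, the correlation of arm with date is 0.865, and the variance of the arm estimate rises by 1/(1 − 0.865²), about 4. A step change between periods would still be missed. The protocol does not describe such a term.

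**4. What the planned model does remove.**
- A stable difference in level already present at T0 cancels in a group-by-visit contrast.
- Drift in measured case mix can be partly adjusted. The P<0.01 entry rule limits this: with 40 per arm, a continuous covariate must differ by about 2.64 × √(2/40) = 0.59 SD to qualify.
- A period effect on change after baseline that does not run through those covariates stays in full.

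**5. Size of the effect on the error rate.** Evaluable per arm: 40 × (1 − 0.15) = 34 (Sample size section). In SDs of change, SE = √(2/34) = 0.243. With no programme effect and a shift b in change, the two-sided rejection rate is Φ(b/SE − 1.96) + Φ(−b/SE − 1.96):

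| Assumed shift in change | Rejection rate |
|---|---|
| 0 | 5% |
| 0.2 SD | 13.1% |
| 0.3 SD | 23.6% |
| 0.4 SD | 37.8% |

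A small GEE simulation (300 runs per scenario, 34 per arm, within-person correlation 0.5, no programme effect) agrees: shifts of 0.3 and 0.5 SD gave mean group-by-visit estimates of 0.28 and 0.49 SD. The covariate in it was unrelated to outcome, so it shows only that the shift passes through. It does not test case-mix adjustment.

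**6. How small a shift would matter.** A trial with 80% power that observes exactly its design effect has an estimate of (1.96 + 0.84) × SE. The lower 95% limit is then 0.84 × 0.243 = 0.20 SD. On that result, a favourable period shift of about 0.20 SD would bring the limit to zero.

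**The case against.** **The risk is disclosed, and mitigating is not eliminating.** This is fair. The protocol names secular trends, calls the design quasi-experimental throughout, and explains why concurrent enrolment was rejected. It hides nothing. The fault is in the stated cure.

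**It is too strong to say that no model can help.** This stands in part. A reader might infer that covariate-adjusted GEE does nothing at all about time trends. The documents do not support that, because measured case-mix drift and a stable baseline difference are both addressed to some degree and a linear date term is estimable by extrapolation.

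**Season.** A reader might also infer that the arms are seasonally opposed at every visit. They are not: October falls in both recruitment windows. The seasonal imbalance is real but partial.

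**The percentages are tied to a simple model.** This is correct. They hold for a shift in post-baseline change, in SDs of change, with 34 per arm. They do not hold for a shift already present at T0. The plan is also intention-to-treat with imputation, so the analysed number may differ from 34.

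**Results would not necessarily be claimed as efficacy.** Also correct. The Discussion and Conclusion are worded conditionally, and an adverse trend would hide a benefit.

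**Sensitivity analyses belong in the analysis plan.** Their absence is not the point here. The point is an affirmative statement that the recruitment windows contradict, and no later plan can create overlap.

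**Conclusion.** The concern holds in a limited form. Arm and enrolment period are completely aliased. For any period effect on post-baseline change that measured baseline characteristics do not carry, neither adjusted GEE nor standardised delivery provides the mitigation claimed. Training staff and holding regular team discussions keep the programme consistent, but they do not equate the two periods.

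Whether such an effect occurred is unknown, and so is its direction. If one of 0.2 to 0.4 SD of change favoured the later period, the false-positive rate would be about 13% to 38% in place of 5%. This rests on the assumed shifts, 34 evaluable per arm and a normal approximation. The choice of a non-randomised design is not challenged. The point concerns what the analysis is said to achieve and what may be concluded from it.

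**What to change.** 1. In Limitations, restrict the mitigation claim to imbalance in measured baseline characteristics, and take secular trends out of what GEE and standardised delivery are said to address.
2. State that arm and enrolment period are aliased, so the group effect cannot be separated from period effects on change. Word the conclusions accordingly.
3. Report the period shift in change, in C-PSOC points and in SD, that would bring the lower confidence limit of the group effect to zero. This needs no new data.
4. Optionally, show within-cohort trends by recruitment month, descriptively and with confidence intervals. They must not be used as evidence that no period effect exists. With even accrual and 34 per cohort, the pooled slope carried across the 6.5 months between cohort midpoints has SE 6.5/√(34 × 6²/12 + 34 × 7²/12) = 0.42 SD, a 95% half-width of about 0.8 SD, and it is blind to a step change.

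The cost is a few sentences and one small calculation. The downside is a more cautious conclusion.

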### Practice implications

The PSE program has the potential to effectively improve parental self-efficacy, treatment compliance, FQoL, and reduce parenting stress and symptom severity in parents and children, respectively. This study can assist pediatric nurses in enhancing early intervention for parents of children with ASD, as they can serve as a manager in multidisciplinary cooperation and resource integration. The study also provides evidence supporting the use of both face-to-face and online sessions in family interventions for parents of children with ASD. Future studies could explore differences in the effects of implementing interventions across different demographic and cultural contexts, providing insights into the development of interventions for parents of children with ASD.

## Conclusion

If the expected results are obtained, the findings of this study will contribute to the development of methods and strategies to improve parental self-efficacy for parents of children with ASD in the early stage of diagnosis. This will be valuable for nurses and healthcare professionals working with this population.
